### Intervention

TMD treatment is multifactorial, and is provided by dentists and physical therapists. It consists of patient education on normal jaw function, avoidance of overuse in oral ‘bad habits’ such as nail biting and tooth clenching. In case of grinding, night time use of stabilisation splints can be applied. Bothersome malocclusions will be addressed, e.g. by providing stabilisation splints. Patients are encouraged to relax their masticatory muscles, and relaxation of the muscles will be trained. Painful muscles will be stretched, wherein stretching techniques will be instructed to the patients so they can continue these exercises at home. During every physical therapy session, these exercises will be boosted to enhance patient compliance [40]. In total, the treatment period can last up to 9 weeks. This is longer than the traditional 6 weeks, yet it is based on our previous trial concerning cervicogenic somatic tinnitus, where an increase of complaints was observed after 6 weeks of therapy [6]. We therefore provide 3 additional weeks where the patient can be followed-up by the treating healthcare professional. Depending on the needs, up to 18 physical therapy sessions can be scheduled over a period of 9 weeks; two sessions per week for the first 3 weeks, one session per week for the next 6 weeks, and optional additional sessions to monitor patient compliance.

Trained clinicians will provide treatment. All participating clinicians are trained in the treatment protocol by the researchers. Patients with tinnitus attributed to a TMD will be referred to the trained clinicians for TMD treatment (guided referral).

### Sample size and power

The primary outcome measure, the TQ, will be used to investigate differences between the direct-start group and delayed-start group in week 9 of the study. We plan to include patients in both groups in a 1:1 ratio. Based on literature data [31], we expect a minimal significant decrease in TQ score of 8.72 points (SD 13.72). To be able to reject the null hypothesis that the population means of the direct-start group and delayed-start group in week 9 are equal with probability (power) of 0.8, we will need to study 37 patients in each group. The Type I error probability associated with this test of this null hypothesis is 0.05.

This sample size will be refined after a pilot study containing 2 × 5 patients. Considering the possibility of dropouts and the later analysis of prognostic indicators and mediation analysis, we aim to recruit 2 × 100 patients.

The primary analysis population is the intention-to-treat population. This population includes all randomised patients who provided baseline data, regardless of whether or not they adhere to the complete protocol.

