### Outcome measures

#### Primary outcome measure

The primary outcome measure is change in tinnitus-related distress, measured using the Dutch version of the TQ, validated in 2007 [29, 30]. The TQ consists of 52 questions, of which 40 are used for calculating the total score and 2 are counted double (items 5 and 20). The questions are answered on a 3-point scale, ranging from ‘true’ (scoring 0) to ‘partly true’ (scoring 1) to ‘not true’ (scoring 2). The total score on the TQ ranges from 0 to 84. Higher scores correspond with higher tinnitus-related distress. The TQ shows high internal consistency (Cronbach’s alpha: 0.95) and a good correlation with the Tinnitus Handicap Inventory and Tinnitus Impairment Questionnaire (0.83–0.90) [31]. A decrease of 8.72 points is considered as clinically relevant (standardised response mean 1.04) [31].

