### Statistics

Our null hypothesis is that the change in TQ at week 9 is equal in both groups (early-start and delayed-start):

H_0_: Change in TQ-baseline to TQ-9 weeks (early start) = Change in TQ-baseline to TQ-9 weeks (delayed start).

The primary outcome is a change in the scores on the TQ after 9 weeks of treatment. The mean change in TQ score between baseline and 9-week (post treatment) scores will be calculated. This mean change in TQ of the early start group will be compared to the mean change in TQ of the delayed-start group that has not yet received treatment at this point. A difference between both groups will be defined as statistically significant when *p* < 0.05.

A repeated measures ANOVA and post-hoc tests will be used to compare the mean changes of the early-start group and delayed-start group at 9 weeks, and secondary at baseline, 18, and 27 weeks follow-up. The same cut-off point of *p* < 0.05 will be used here.

For the mediation analysis, the protocol described by Baron and Kenny [41] will be used to calculate the role of potential contributing factors in the obtained output. This implies the execution of three regression analyses. The first will assess the relation between the applied therapy (independent variable) and the outcome (dependent variable). The second will assess the relation between the applied therapy (independent) and a mediating factor to confirm that the applied treatment significantly affects the mediator. The third will be used to confirm that the mediator significantly predicts the treatment outcome (dependent variable), while controlling for the applied treatment (independent variable). Again, a cut-off point of *p* < 0.05 will be used.

Bootstrapping will be performed to avoid overestimation of the mediation effect. As potential mediating factors, all secondary outcome measures will be used.

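### The stated 37 per group falls slightly short of 80% power on the protocol's own inputs, and the calculation does not say whether its SD is of TQ scores or of change

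*Protocol article*

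**What the plan says.** All from the protocol article.

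- *Sample size and power*, effect and spread: "we expect a minimal significant decrease in TQ score of 8.72 points (SD 13.72").
- Same section, allocation: "We plan to include patients in both groups in a 1:1 ratio".
- Same section, error rates: the hypothesis is that the two groups' population means "in week 9 are equal with probability (power) of 0.8" to reject it, and "The Type I error probability associated with this test of this null hypothesis is 0.05".
- Same section, result: "we will need to study 37 patients in each group". The section adds that this number will be revisited after a pilot of 2 × 5 patients, and that the recruitment aim is 2 × 100, to allow for dropout and for the prognostic and mediation analyses.
- *Statistics*, primary hypothesis: "Our null hypothesis is that the change in TQ at week 9 is equal in both groups". The formula beneath it is written on change from baseline to week 9.
- *Primary outcome measure*: "A decrease of 8.72 points is considered as clinically relevant (standardised response mean 1.04").

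**The concern.** Two things do not fit.

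First, the effect, SD, alpha, power and allocation are all given, so the number per group can be recomputed, and the result is not 37. The difference is in the unsafe direction: the stated number has less power than claimed.

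Second, the calculation is framed as a comparison of week-9 means, while the primary hypothesis concerns change from baseline. Under randomisation both target the same treatment effect, so the numerator of 8.72 can serve either. The SD cannot, in general. With equal variances at the two visits, the SD of a score and the SD of its change coincide only when the baseline to week-9 correlation is 0.5. The protocol gives no correlation and does not label 13.72.

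At stake is whether a reader can tell which test has 80% power, and whether the announced recalculation starts from a defined test and a defined SD.

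**Working it through.** **Inputs.** From *Sample size and power*: difference δ = 8.72, SD σ = 13.72, α = 0.05, power 0.80, ratio 1:1. Sidedness is not stated. I take two-sided, because the null is equality and the Statistics section counts a difference in either direction ("A difference between both groups will be defined as statistically significant when" p < 0.05).

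**Step 1. Try to reproduce 37.**

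Standardised difference: d = 8.72 / 13.72 = 0.6356, and d² = 0.4039.

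Normal approximation, two-sided: n = 2(1.960 + 0.842)² / d² = 38.86, so **39** per group.

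Two-sample t-test (noncentral t), two-sided: the smallest n with power of at least 0.80 is **40** per group.

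One-sided test: 31 (normal approximation) or 32 (t-test). A paired one-sample calculation gives 22. None of these variants returns 37.

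**Step 2. Power at the stated number.** At n = 37 the standard error of the difference is 13.72 × √(2/37) = 3.190, so the noncentrality is 8.72 / 3.190 = 2.734.

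| n per group | t-test | normal approximation |
|---|---|---|
| 37 | 76.9% | 78.0% |
| 39 | 79.1% | 80.1% |
| 40 | 80.2% | 81.1% |
| 100 | 99.4% | 99.4% |

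The shortfall is 2 to 3 patients per group, or 2 to 3 percentage points of power.

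**Step 3. What the unlabelled SD does.** Write r for the correlation between baseline and week-9 TQ, and assume equal variances at the two visits. The protocol gives no r, so the values below are assumptions.

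*If 13.72 is the SD of change*, it fits the primary null directly, and Steps 1 and 2 apply: 40 per group, or 77% power at 37.

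*If 13.72 is the SD of scores*, the SD of change is 13.72 × √(2(1 − r)), and the test of change (two-sided t-test) behaves as follows:

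| assumed r | SD of change | n per group for 80% | power at 37 |
|---|---|---|---|
| 0.3 | 16.23 | 56 | 63% |
| 0.5 | 13.72 | 40 | 77% |
| 0.6 | 12.27 | 33 | 85% |
| 0.7 | 10.63 | 25 | 94% |

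So the label matters more than the arithmetic slip, and it can move the answer either way.

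**The case against.** The strongest reply is that nothing turns on 37. The section calls it provisional, a recalculation is announced, and the recruitment aim is 100 per group. On the stated inputs that aim gives 99.4% power, and even 50 evaluable patients per group would give 88%. By the normal approximation, 37 is only two patients and about two points of power short. It can also be said that the mismatch in hypotheses is mostly wording: the sample-size paragraph itself speaks of a decrease in TQ, and the Statistics section writes out the null on change, so the primary test can be identified. All of this stands, and it is why the point is minor. It does not make 37 the right answer to the calculation as stated, nor does it label the SD.

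Three stronger readings are tempting, and the protocol does not support them.

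- *The primary analysis is underpowered.* A reader could take 13.72 as the SD of change, power a comparison of raw week-9 means, and obtain 67% to 55% at 37 per group for correlations of 0.6 to 0.7. That is not the primary test. The opposite reading gives 85% to 94% at the same correlations.
- *The standardised response mean shows 13.72 to be wrong.* Dividing 8.72 by 1.04 gives 8.38, but that is an SD of change only if 8.72 is the mean change in the patients from whom 1.04 was calculated. The protocol calls 8.72 a clinically relevant decrease and does not say this.
- *37 is the base for the recalculation.* The protocol does not say what the recalculation starts from.

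**Conclusion.** Minor, but wrong as written. On the protocol's own inputs, with alpha taken as two-sided, 80% power needs 40 per group by the t-test (39 by the normal approximation), and 37 gives about 77% (78%).

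The paragraph is also worded for a different null from the primary one, with an SD whose meaning is left open. If 13.72 describes change, the error is confined to those 2 to 3 patients. If it describes scores, power for the primary test at 37 cannot be fixed without a correlation; that range rests on assumed correlations and on equal variances at the two visits.

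It would be wrong to infer that the trial as planned is too small. The finding concerns the stated justification, not the recruitment aim.

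**What to change.** 1. Confirm from the cited source whether 13.72 is an SD of TQ scores or of change in TQ, and say so. The protocol does not settle this, so neither label should be adopted without that check.
2. Write the calculation for the null in the Statistics section (equal change from baseline to week 9), and state that alpha is two-sided if that is intended.
3. Restate the result. If 13.72 is the SD of change, either give 40 evaluable patients per group for 80% power, or keep 37 and give its power as 77%. If it is the SD of scores, state the assumed correlation and recompute.

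The cost is one revised paragraph and a look at the source. No extra patients are needed on the stated inputs, and the recruitment aim of 2 × 100 can stand.

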### Statistics

Our null hypothesis is that the change in TQ at week 9 is equal in both groups (early-start and delayed-start):

H_0_: Change in TQ-baseline to TQ-9 weeks (early start) = Change in TQ-baseline to TQ-9 weeks (delayed start).

The primary outcome is a change in the scores on the TQ after 9 weeks of treatment. The mean change in TQ score between baseline and 9-week (post treatment) scores will be calculated. This mean change in TQ of the early start group will be compared to the mean change in TQ of the delayed-start group that has not yet received treatment at this point. A difference between both groups will be defined as statistically significant when *p* < 0.05.

A repeated measures ANOVA and post-hoc tests will be used to compare the mean changes of the early-start group and delayed-start group at 9 weeks, and secondary at baseline, 18, and 27 weeks follow-up. The same cut-off point of *p* < 0.05 will be used here.

For the mediation analysis, the protocol described by Baron and Kenny [41] will be used to calculate the role of potential contributing factors in the obtained output. This implies the execution of three regression analyses. The first will assess the relation between the applied therapy (independent variable) and the outcome (dependent variable). The second will assess the relation between the applied therapy (independent) and a mediating factor to confirm that the applied treatment significantly affects the mediator. The third will be used to confirm that the mediator significantly predicts the treatment outcome (dependent variable), while controlling for the applied treatment (independent variable). Again, a cut-off point of *p* < 0.05 will be used.

Bootstrapping will be performed to avoid overestimation of the mediation effect. As potential mediating factors, all secondary outcome measures will be used.

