### Randomisation procedure

Patients will be randomised into the early-start group or into the delayed-start group in a 1:1 ratio insuring an even distribution based on sex and age. The randomised list will be generated by an independent researcher using QMinim Online Minimisation® [28]. The assessor performing the clinical tests is blinded to the allocation of the patients in the direct-start or delayed-start group. This is possible because all patients are investigated 18 weeks after the start of their therapy (Fig. 1). The extra measurements in the delayed-start group, in week 18 of the study, are questionnaires that are completed via an online tool. Patients cannot be blinded in this protocol.

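### The primary comparison of unadjusted TQ changes is valid but less precise than an analysis adjusted for baseline TQ, sex and age, all of which the trial already holds

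*Protocol article*

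**What the plan says.** The Statistics section of the protocol article sets the primary null hypothesis in terms of change: "Our null hypothesis is that the change in TQ at week 9 is equal in both groups". It then describes the comparison: "This mean change in TQ of the early start group will be compared to the mean change in TQ of the delayed-start group". The model it names is this: "A repeated measures ANOVA and post-hoc tests will be used to compare the mean changes of the early-start group and delayed-start group at 9 weeks". Neither statement includes a covariate. The only regression in that section that controls for anything belongs to the mediation analysis.

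The Randomisation procedure section allocates patients "in a 1:1 ratio insuring an even distribution based on sex and age", by minimisation: "The randomised list will be generated by an independent researcher using QMinim Online Minimisation". Baseline TQ is not a balancing factor.

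The Sample size and power section words the null hypothesis differently, as the "null hypothesis that the population means of the direct-start group and delayed-start group in week 9 are equal". Its input is "we expect a minimal significant decrease in TQ score of 8.72 points (SD 13.72"), without saying whether the SD is that of the change or of the week-9 score. It derives 37 per group for 80% power at a type I error of 0.05, and aims to recruit 100 per group. Table 2 lists TQ at baseline, and the intention-to-treat definition relies on baseline data: "This population includes all randomised patients who provided baseline data".

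**The concern.** Subtracting the baseline score assumes that each extra point of TQ at baseline carries forward as one extra point at week 9. When the correlation is below 1 and the SDs at the two visits are similar, the true slope is below 1 and the subtraction over-corrects. Two things follow. The treatment difference has a larger variance than it needs to have. A chance gap in baseline TQ between the arms, which minimisation on sex and age does not control, also pulls the realised estimate in the direction of regression to the mean.

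Separately, minimisation makes the arms more alike on sex and age than simple randomisation would. If those factors predict TQ, an analysis that leaves them out does not credit that balance, so its standard error is too large and its test conservative.

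What is at stake is precision and robustness to chance imbalance. The validity of the trial is not in question.

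**Working it through.** **Inputs.** From Sample size and power: difference 8.72 points, SD 13.72, power 0.80, alpha 0.05, 1:1 allocation, 37 per group required, 100 per group aimed for. Assumed: a two-sided test (sidedness is not stated), equal TQ SDs at baseline and week 9, and rho = 0.5, 0.7 or 0.9 (the article gives no value).

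**The plan's own figure.** n per group = 2 × [SD × (1.960 + 0.842) / difference]² = 2 × (13.72 × 2.802 / 8.72)² = 38.86, so 39. A noncentral t calculation gives 40. The stated 37 is close. At 37 per group the power is 0.78 by the normal approximation and 0.77 by t. The small shortfall is not the point here.

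**What the named model does.** Over baseline and week 9, the group-by-time contrast of a repeated measures ANOVA is the difference between arms in mean change. Naming that model therefore does not change the estimator.

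**Variance.** With score variance σ² at both visits:
- change score: 2σ²(1 − rho)
- ANCOVA: σ²(1 − rho²)
- ratio, ANCOVA to change score: (1 + rho)/2

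**Results if 13.72 is the SD of change** (normal approximation):

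| | Change score | ANCOVA, rho 0.5 | rho 0.7 | rho 0.9 |
|---|---|---|---|---|
| Variance ratio | 1 | 0.75 | 0.85 | 0.95 |
| Residual SD | 13.72 | 11.88 | 12.65 | 13.37 |
| n per group, 80% power | 39 | 30 | 34 | 37 |
| Power at 37 per group | 0.78 | 0.88 | 0.84 | 0.80 |
| Power at 100 per group | 0.994 | 0.999 | 0.998 | 0.996 |
| Difference detectable with 80% power at 100 per group | 5.44 | 4.71 | 5.01 | 5.30 |

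The width of the confidence interval scales with the square root of the variance ratio: 0.866, 0.922 and 0.975. The interval is therefore about 13%, 8% or 3% narrower.

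**If 13.72 is instead the SD of the week-9 score**, the change-score SD is 13.72 × √[2(1 − rho)]. The n per group, change score against ANCOVA, is 39 against 30 at rho 0.5, 24 against 20 at 0.7, and 8 against 8 at 0.9. A plain comparison of week-9 means needs 39 whatever rho is. It matches the change score only at rho 0.5, where σ² = 2σ²(1 − rho). This is why the meaning of the SD has to be stated.

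**Chance baseline imbalance.** A baseline gap of D points shifts the expected change-score difference by (1 − rho)D. For illustration, take a TQ score SD of 13.72. One standard error of the baseline gap is 13.72 × √(2/37) = 3.2 points at 37 per group and 13.72 × √(2/100) = 1.9 points at 100 per group. At rho 0.5 and 0.7 the shift is about 1.6 and 1.0 points with 37 per group, and about 1.0 and 0.6 with 100 per group, against a target of 8.72.

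**Sex and age.** The article gives nothing from which to size this. If they explained an assumed further 0 to 10% of the residual variance, n at rho 0.7 would go from 34 (38.86 × 0.85 = 33.0) to 30 (33.0 × 0.90 = 29.7).

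**The case against.** Several things can fairly be said for the plan.

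- A reader might infer that the analysis ignores baseline TQ. It does not: baseline is subtracted from every patient's score. Only the slope is at issue.
- A reader might infer that the estimate is biased. Under randomisation the change-score difference is unbiased. The shift described above is conditional on an imbalance that happens to occur.
- A reader might infer that the trial is under-powered. At 100 per group it is not, with or without adjustment, if 13.72 is the SD of change.
- A reader might infer that the two sections pursue different estimands. Baseline means are equal in expectation, so equal week-9 means and equal changes concern the same treatment difference. The mismatch is one of wording and variance.
- Rho may be high. Tinnitus must have been stable for at least 3 months, so values of 0.8 to 0.9 over 9 weeks are plausible, although undocumented. The variance saving would then be only 10% to 5%.
- Nothing in the article shows that sex or age is prognostic, and a covariate list is ordinary content for an analysis plan that is not shown.

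All of this stands, and it limits the size of the point. It does not remove it. The change-score comparison is stated positively as the primary analysis, so it is more than a gap that a later document might fill. The 100 per group is an aim, justified by dropouts and the secondary analyses, and the sample size is to be refined after the pilot. If recruitment ended near 37 per group, the choice of estimator could decide whether 80% power is reached.

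**Conclusion.** The point holds as a modest loss of efficiency in a valid analysis. For any rho below 1, ANCOVA is more precise than the stated comparison. Where the trial ends between 37 and 100 per group decides whether the benefit shows mainly as power or as a narrower interval; protection against a chance baseline gap comes in either case. The sizes rest on equal SDs at the two visits, an assumed rho of 0.5 to 0.9 and a two-sided test. The power figures also take 13.72 as the SD of change. The contribution of sex and age cannot be quantified from the article and may be near zero. If they are prognostic, leaving them out makes the standard error too large, so the error is on the conservative side.

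**What to change.** In the Statistics section, define the primary analysis as an ANCOVA (or equivalent mixed model) of week-9 TQ on treatment arm, with baseline TQ, age and sex as covariates. Report the adjusted difference between arms with its 95% confidence interval. Modelling the change instead of the week-9 score gives the same treatment estimate once baseline is in the model, so the clinical description in terms of change can stay.

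In Sample size and power, word the null hypothesis to match, and state whether 13.72 is the SD of the change or of the week-9 score. The planned recalculation after the pilot is a natural place to do this.

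The cost is about one sentence in each section. Baseline TQ is already collected, and age and sex are already needed for allocation. The change should be made before outcome data are analysed.

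### Mediation rests on the Baron and Kenny p-values, not on the indirect effect; if the total-effect step acts as a gate, true mediators are often missed when the TQ effect is well below plan

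*Protocol article*

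**What the plan says.** The Statistics section of the protocol article states that "the protocol described by Baron and Kenny [41] will be used to calculate the role of potential contributing factors". It then sets out the steps: "This implies the execution of three regression analyses".

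- Step 1, total effect: "The first will assess the relation between the applied therapy (independent variable) and the outcome (dependent variable").
- Step 2, therapy on mediator (path a): its purpose is "to confirm that the applied treatment significantly affects the mediator".
- Step 3, mediator on outcome given therapy (path b): it is used to "confirm that the mediator significantly predicts the treatment outcome (dependent variable), while controlling for the applied treatment".

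The criterion follows: "Again, a cut-off point of *p* < 0.05 will be used". A separate paragraph adds: "Bootstrapping will be performed to avoid overestimation of the mediation effect".

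Steps 2 and 3 are worded as tests that must come out significant. Step 1 is worded more loosely. The indirect effect a × b is not named as the quantity that decides, and no interval for it is tied to a decision.

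**The concern.** Identifying mediators is a declared secondary aim (Background). The Discussion defends it again, and the Sample size and power section gives it as one reason for recruiting 2 × 100 patients rather than 37 per group. The mediated effect is the product a × b, but the stated criteria are p-values from three regressions, none of which estimates that product.

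Two consequences follow. First, if step 1 must be significant, the power of the total-effect test caps the power of the whole procedure. A jaw variable that therapy clearly moves, and that clearly predicts TQ, is discarded when the total TQ effect just misses 0.05. Secondly, the bootstrap, which could supply an interval for a × b, is given a different job. Resampling describes the uncertainty of an estimate; a percentile interval does not shrink the estimate or protect it from being too large.

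**Working it through.** **The plan's own figure.** Inputs from Sample size and power: difference 8.72, SD 13.72, power 0.80, alpha 0.05 (taken as two-sided), allocation 1:1.

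n per group = 2 × [13.72 × (1.960 + 0.842) / 8.72]² = 38.86, so 39. The exact t-test gives 40. The stated 37 is close (power 0.78 by the normal formula, 0.77 by the t-test), and nothing below depends on the gap. The article gives no power for mediation.

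**Assumptions.** The article gives no path sizes. Assume standardised a = 0.5 and b = 0.4, with 1 SD = 13.72 TQ points. The indirect effect is then 0.5 × 0.4 = 0.2 SD = 2.7 points. Total effects examined: 0.2 SD (2.7 points, fully mediated), 0.3 SD (0.3 × 13.72 = 4.1 points) and 0.64 SD (8.8 points, about the planned 8.72).

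**Power of each step at 100 per arm** (two-sided t-test, critical value 1.972):

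- Step 1: noncentrality = d × √(100/2). For d = 0.2 it is 1.41, power 0.29. For d = 0.3 it is 2.12, power 0.56. For d = 8.72/13.72 = 0.636 it is 4.49, power 0.994.
- Step 2: 0.5 × √50 = 3.54, power 0.94.
- Step 3: about 0.4 × √198 / √(1 − 0.16) = 6.14, power above 0.99.

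Paths a and b are therefore jointly significant in about 94% of trials whatever the total effect. All three steps cannot pass more often than step 1 does.

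**Simulation of the full rule** (3,000 trials per setting, linear models; a repeat with 6,000 trials agreed within about one percentage point):

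| Per arm | Total effect | a and b both significant | All three steps significant |
|---|---|---|---|
| 100 | 2.7 points | 94% | 28% |
| 100 | 4.1 points | 94% | 54% |
| 100 | 8.8 points | 94% | 94% |
| 37 | 2.7 points | 54% | 11% |
| 37 | 4.1 points | 54% | 18% |
| 37 | 8.8 points | 54% | 46% |

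**Where the loss comes from.** A second simulation (1,000 trials per setting, 400 bootstrap resamples, SD 13.72, 100 per arm) adds a percentile bootstrap interval for a × b. Here a is in SD units of the mediator, and b is set by the share of the total effect that is mediated.

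| Total effect | Share mediated | a | Three steps | a and b jointly | Bootstrap interval |
|---|---|---|---|---|---|
| 8.72 | half | 0.5 | 0.916 | 0.918 | 0.924 |
| 8.72 | half | 0.8 | 0.991 | 1.000 | 1.000 |
| 4.36 | all | 0.5 | 0.580 | 0.948 | 0.952 |
| 4.36 | all | 0.8 | 0.622 | 1.000 | 1.000 |
| 3 | all | 0.5 | 0.329 | 0.934 | 0.938 |
| 3 | all | 0.8 | 0.355 | 0.983 | 0.983 |

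The joint test of a and b and the bootstrap interval agree closely in every row. The fall in detection comes from requiring step 1, not from testing the two paths separately.

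**The case against.** The strongest reply is that the gate is not written. Step 1 is only to be assessed, and the common cut-off sets an alpha without saying that a mediator is dropped when step 1 fails. This stands in part: the gate is implied by the named procedure together with the cut-off, and the power figures are conditional on that reading. The text still leaves open whether step 1 decides anything.

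A reader might infer that using several p-values is itself the fault, or that mediators are missed whenever the total effect is modest. Neither is supported. Joint significance of a and b matches the bootstrap interval (0.948 against 0.952), and at 4.1 points with 100 per arm a true mediator is still found about half the time.

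A reader might also infer that no mediated effect will be estimated. That goes too far: the bootstrap sentence refers to a mediation effect, and interval details are commonly left to an analysis plan. What remains is that the one purpose stated for the bootstrap is one it does not serve, while the stated criteria are p-values.

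Finally, looking for mediators only after an effect has been shown is a defensible conservative choice for a secondary analysis, particularly as "As potential mediating factors, all secondary outcome measures will be used". If that is intended, it should be stated as a choice. The losses also arise at total effects at or below about half of the 8.72 points that the article regards as clinically relevant.

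**Conclusion.** The point holds as a low-severity improvement. The article bases mediation on the Baron and Kenny regressions at p < 0.05, does not make the indirect effect the criterion, and assigns the bootstrap a purpose it does not serve.

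If step 1 is a gate, detection of a true mediator at 100 per arm falls from about 94% to 28% at 2.7 points and to 54% at 4.1 points. At the planned effect with 2 × 100 patients the loss is at most about one percentage point. With only 37 per arm some loss appears even near the planned effect (54% to 46%), but that is not the sample intended for mediation.

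These figures rest on assumed path sizes (a = 0.5 and b = 0.4, with a = 0.8 and other shares mediated as variants), linear models and no dropout. They show a range and are not predictions for this trial.

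**What to change.** In the mediation paragraphs of the Statistics section:

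1. For each prespecified mediator, estimate the indirect effect a × b, report it with a percentile bootstrap 95% interval, and declare mediation from that interval.
2. State that the therapy-to-outcome regression is descriptive and not a gate, and report all three regressions as description.
3. Replace the stated purpose of the bootstrap: it provides the interval for the indirect effect. Remove the claim that it avoids overestimation.

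The cost is wording only, because the regressions and the bootstrap are already planned. The downside is that a mediator may be reported when the total effect on TQ is not significant. The report must then say so.
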